# Instant analgesic effect of radial extracorporeal shock wave therapy on primary dysmenorrhoea according to functional magnetic resonance imaging: study protocol for a randomised placebo-controlled trial

**DOI:** 10.1186/s13063-020-4045-5

**Published:** 2020-02-11

**Keywords:** Pain, Primary dysmenorrhoea, Radial extracorporeal shock wave therapy wave, Functional magnetic resonance imaging

## Abstract

**Background:**

Primary dysmenorrhoea (PDM) is defined as a series of pain-dominated symptoms during and after menstruation without organic lesions. Nonsteroidal anti-inflammatory drugs and oral contraceptives are usually recommended as first-line therapy for the clinical treatment of PDM, but their widespread long-term application is controversial. Radial extracorporeal shock wave therapy (rESWT) has been widely applied in musculoskeletal rehabilitation because of its secure and noninvasive characteristics and its confirmed effect in improving pain symptoms. This research seeks to explore the efficacy of rESWT for PDM and the changes in brain function of patients with PDM.

**Methods:**

This clinical research will be a randomised, blind, sham-controlled trial. Thirty-six patients with PDM will be randomly divided into the rESWT group (*n* = 18) and the sham rESWT group (*n* = 18). In the rESWT group, treatment will be applied once within 48 h of menstruation at six abdominal myofascial trigger points. The sham rESWT group will receive sham shockwave therapy on the same sites but without energy input. Other dysmenorrhoea-related treatments in both groups will be limited. The main indicators include the short form of the McGill Pain Questionnaire and the Cox Menstrual Symptom Scale. The secondary indicators include the Zung Self-rating Anxiety Scale and Self-rating Depression Scale and functional magnetic resonance imaging (fMRI) changes in brain regions. Results will be evaluated at the screening, at baseline, and before and after treatment, and adverse treatments will be examined. Inter- and intragroup analyses will be performed.

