### Outcome measurements

#### Primary outcomes

##### SF-MPQ

The primary outcome will be the change in the short form of the McGill Pain Questionnaire (SF-MPQ) score (Table 1). The SF-MPQ is a scale composed of a pain rating index, a visual analogue scale and existing pain intensity to measure pain intensity. The pain rating index consists of 11 sensory and 4 emotional pain descriptors, all of which are rated from 0 to 3 points to indicate the different degrees of no, mild, medium, or severe pain, respectively. This index is a sensitive and reliable pain evaluation method widely used in the assessment of dysmenorrhoea [18].

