##### CMSS

The menstrual pain symptoms of participants will be integrally evaluated by the Cox Menstrual Symptom Scale (CMSS), which consists of 18 items or symptoms, including cramps, nausea, vomiting, loss of appetite, headaches, backaches, leg aches, dizziness, weakness, diarrhoea, facial blemishes, abdominal pain, flushing, sleeplessness, general aching, depression, irritability, and nervousness [19]. The scale is mainly used to evaluate the severity and duration of menstrual pain symptoms. All items use a five-level scoring method ranging from 0 to 4 points. The choices for pain severity include painless, mild pain, moderate pain, severe pain, and very serious pain. Patients can evaluate the duration of their pain as 0 h, less than 3 h, 3–7 h, 7–24 h and more than 24 h. The CMSS will be used before and after rESWT treatment.

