##### SDS

The Self-rating Depression Scale (SDS) is a scale used to evaluate changes in terms of depression [20]. In this trial, participants will fill out 20 items based on their actual experience over the past week. The total score for this scale ranges from 20 to 80, with a score above 40 indicating depressive symptoms. This scale will be employed before and after rESWT treatment (Table 1).

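### The primary outcome is defined inconsistently (SF-MPQ alone, or SF-MPQ and CMSS), and no rule says which result decides efficacy at p < 0.05

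*Protocol article*

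**What the plan says.** The places that bear on the primary outcome do not agree.

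- Abstract, Methods: "The main indicators include the short form of the McGill Pain Questionnaire and the Cox Menstrual Symptom Scale". Two instruments, with no order between them.
- Primary outcomes, SF-MPQ: "The primary outcome will be the change in the short form of the McGill Pain Questionnaire (SF-MPQ) score". This is singular and does not mention the CMSS. The same section adds: "The SF-MPQ is a scale composed of a pain rating index, a visual analogue scale and existing pain intensity to measure pain intensity". No component is called the lead score and no combining rule is given.
- Primary outcomes, CMSS: the scale stands under the same plural heading. "The scale is mainly used to evaluate the severity and duration of menstrual pain symptoms", which makes two aspects. On duration, patients "evaluate the duration of their pain as 0 h, less than 3 h, 3–7 h, 7–24 h and more than 24 h". On timing: "The CMSS will be used before and after rESWT treatment".
- Discussion: the CMSS is again described as one of the main outcome measures.
- Statistical analysis: all tests are two-sided and p < 0.05 is significant. The between-group t test concerns relief of PDM, but the outcome it is applied to is not named. No hierarchy, joint-success rule or adjustment is given.
- Sample size calculation: this rests on effectiveness proportions of 0.8 and 0.45. No outcome in the article is defined as such a proportion.

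Among the secondary outcomes, the SDS has a recall period: "participants will fill out 20 items based on their actual experience over the past week". The title and the Abstract's Discussion paragraph state the target as an instant or immediate effect of a single session.

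**The concern.** A reader of the results needs to know beforehand which comparison decides whether rESWT works. Here the SF-MPQ section points to one instrument, three other places point to two, and the sample size points to neither. With a blanket 5% threshold, a favourable SF-MPQ result, a favourable CMSS result, or one component of either could be presented as the primary finding without departing from the text. The error rate of the efficacy claim is then above the stated 5%.

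There is also a question of fit. A duration item graded up to more than 24 hours and a past-week depression scale look back over time that lies largely before a short post-treatment assessment. They may say little about an immediate effect, in either direction.

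**Working it through.** **Inputs.** Significance level 0.05, two-sided, for each test (Statistical analysis). Two primary instruments (Abstract; SF-MPQ and CMSS sections). Component scores counted from the instrument descriptions: SF-MPQ 3 (pain rating index, visual analogue scale, existing pain intensity) plus CMSS 2 (severity, duration) = 5. The article does not list these five as separate tests. Correlations between scores are not given, so they are assumed over a range.

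**The plan's own rate.** With one test, 1 − 0.95 = 5%. The stated level holds only if a single score is designated.

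**Any one success suffices, independent scores.** Rate = 1 − 0.95^k.

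- k = 2: 1 − 0.95² = 1 − 0.9025 = 9.75%
- k = 5: 1 − 0.95⁵ = 1 − 0.7738 = 22.6%

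**Correlated scores.** Under the null, test statistics were simulated as √ρ·F + √(1−ρ)·Eᵢ with F and Eᵢ standard normal (400,000 draws). A false positive is any |statistic| above 1.96.

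| Assumed ρ | 2 instruments | 5 scores |
|---|---|---|
| 0 (formula) | 9.75% | 22.6% |
| 0.5 | 9.1% | 18.2% |
| 0.7 | 8.3% | 14.9% |
| 0.9 | 7.1% | 10.2% |

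Only between-group tests are counted. The within-group before-and-after tests in the same section are left out.

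**Both instruments must succeed.** The error rate would then not exceed 5%, but power would fall. No such rule is stated.

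**Timing of CMSS duration and SDS.** Table 1 places the CMSS, SAS and SDS at the two MRI scans, before and after treatment, all under the same one-month heading. It gives no hours. The 48 hours in the Interventions section is the window for treatment, not for the questionnaires. A short gap follows only from the stated aim of an immediate effect. Given a short gap, there are two ways to read CMSS duration:

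- If it counts hours of pain in the current menses, hours already accrued cannot fall, so the score stays or rises within each arm. The arms can still differ if pain stops in one and continues in the other, but a short gap leaves little room for that.
- If it counts only hours since treatment, the post-treatment score covers a different period from the baseline score.

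For the SDS, if the two forms were completed within one day (an assumption), at least 6/7 = 86% of the recall week would be shared.

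**The case against.** The strongest reply is that this is a condensed article, that scoring and multiplicity rules commonly sit in a full protocol or analysis plan, and that the Discussion calls the trial exploratory. That disposes of any complaint that an adjustment procedure is missing. It does not remove the conflict within the article over which outcome is primary, and the first objective is to evaluate efficacy.

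Four stronger readings might be inferred, and the documents do not support them.

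- That five primary tests are planned, each at 0.05, so the error rate is several times 5%. The five are a count of components. The SF-MPQ section speaks of a score in the singular, and the plain reading is two instruments. All the scores rate the same menstrual pain or symptoms, so independence is unlikely and 22.6% is a ceiling.
- That Table 1 puts both CMSS readings within the first 48 hours of menses. It does not, and the figure showing the procedure is not available in the text.
- That CMSS duration cannot register an effect at all. Because randomised arms are compared, a difference in accrued hours remains possible. The case is one of low sensitivity, and it does not touch CMSS severity, the visual analogue scale or existing pain intensity.
- That the SDS adds to the primary multiplicity. It is a secondary outcome and bears only on the recall question.

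**Conclusion.** The point stands in limited form. The article defines its primary outcome inconsistently and gives no rule for what counts as success. If either instrument can support the efficacy claim, the false-positive rate is about 8–10%: 9.75% under independence and 8.3–9.1% at assumed correlations of 0.7 to 0.5. If the component scores were each tested, it would be about 10–18% at assumed correlations of 0.9 to 0.5, and 22.6% at most. These figures rest on an any-success reading that the text permits but does not state.

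The secondary conclusion is conditional: CMSS duration and the SDS are poorly suited to an immediate effect if the second questionnaire follows soon after the session. The title and Abstract imply this, but the readable text does not give the interval.

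**What to change.** Let the SF-MPQ section govern. Name one present-pain score of that instrument, for example the visual analogue scale, as the sole primary outcome: the change from before to after treatment, compared between groups at two-sided 0.05. Make the remaining SF-MPQ scores and the CMSS secondary, reported with confidence intervals and without an efficacy claim of their own. Align the Abstract, the CMSS section and the Discussion with this. State that CMSS duration and SDS results will not be interpreted as measures of the immediate effect.

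If the sponsor wants to keep both instruments primary, prespecify a fixed sequence or Holm's procedure across the two, with one score named for each. The price can be gauged from the first Holm step at 0.025: with 15 completers per group, the standardised difference detectable with 80% power on a t test rises from 1.06 to 1.18.

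Moving the post-treatment CMSS and SDS to close-out is not recommended. Table 1 gives no date for that contact and no questionnaires at it. The move would replace the immediate-effect question, and it would separate the CMSS from the post-treatment scan, whose results the Discussion wants to relate to change in pain.

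The cost is mainly wording. The CMSS could no longer establish efficacy alone. The sample size, built on a responder proportion, does not correspond to the chosen score and should be restated for it.

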**Discussion:**

This randomised controlled study is designed to explore the immediate efficacy of rESWT for PDM. After rESWT treatment, PDM symptom tests and pain tests, as well as fMRI data, will be investigated for the potential connections between immediate neuroanalgesic mechanisms, which are associated with pain and brain networks. The main results will be used to assess the efficacy of rESWT, and secondary results will focus on improving the neurobiological understanding of disease treatment.

**Trial registration:**

China Clinical Trial Register, ChiCTR1900020678. Registered on 13 January 2019.

## Background

Primary dysmenorrhoea (PDM) involves premenstrual or menstrual pain in the lower abdomen without pelvic organic lesions and may spread to the waist and inner thigh. PDM is also characterised by a series of symptoms such as headache, fatigue and irritability. PDM affects more than 55% of young women worldwide, often with pain so severe that restricts their work and daily activities [1], thus causing considerable personal and socioeconomic burden [2].

Despite the importance of PDM management, clinical treatment is still inadequate. According to the Primary Dysmenorrhea Consensus Guideline, nonsteroidal anti-inflammatory drugs or combined hormonal contraceptives are recommended as first-line treatment for most women with PDM [3]. Nonsteroidal anti-inflammatory drugs hinder the production of peripheral prostaglandins by inhibiting cyclooxygenase, thereby producing analgesic effects [4]. Combined hormonal contraceptives relieve pain by inhibiting ovulation and the growth of endometrial tissue and reducing blood flow and prostaglandins, thus decreasing stress and contractions in the uterus. The analgesic effect of such contraceptives is definite, but long-term use can cause gastrointestinal damage or abnormal hormone secretion. As an alternative treatment, physical factor therapies, such as high-frequency electrical stimulation, ultra-short wave therapy and hot compress [3], have weak practical application because of their obvious side effects, expensive treatment or long treatment cycle and unsatisfactory treatment outcomes.

Radial extracorporeal shock wave therapy (rESWT) involves a kind of mechanical wave that can convert mechanical signals into the target area in vitro into biochemical or molecular signals and induce changes in cell characteristics. A descending pain suppression system that plays a role in analgesia has been accepted all over the world for the extensive treatment of musculoskeletal pain, especially for intractable pain such as chronic periarthritis of the shoulder and stubborn plantar fasciitis [5, 6]. Clinical studies have shown that the acute to chronic transformation of musculoskeletal diseases will lead to a series of peripheral nervous system lesions and even structural changes of the central nervous system, accompanied by different degrees of myofascial trigger point symptoms, such as spontaneous pain and dysmenorrhoea. Moreover, the selection of clinical treatment sites is primarily related to the location of the myofascial trigger point. The clinical study by Huang et al. [7, 8] shows that the pain and related symptoms of PDM can be effectively alleviated in patients with the trigger point of abdominal myofascial pain and who receive local dry and wet acupuncture treatment at the trigger point. Li et al. [9] and Xing [10] confirmed that rESWT can effectively alleviate the symptoms of chronic dysmenorrhoea. In the future, rESWT may be another treatment to complement ibuprofen. However, few studies have been conducted on the immediate analgesic effect of rESWT, and evidence of its central analgesic effect is insufficient.

Tu et al. [11–13] proved that the generation of PDM is related to the abnormal changes in metabolism in brain regions that are related to various aspects of pain management. The major manifestations include increased glucose metabolism in the thalamus, orbitofrontal area and prefrontal area. Conversely, lowered metabolism occurs in the lateral somatosensory motor area. Some imaging studies have confirmed that patients with moderate and severe PDM have structural and functional consistency changes in multiple pain-related brain regions after acupuncture or moxibustion [14–16]. Imaging evidence of functional changes in PDM brain areas is limited by the fact that different interventions have dissimilar effects on brain areas. A recent study [10] showed that rESWT can effectively balance the concentration of blood prostaglandin in women with dysmenorrhoea after the treatment of one menstrual cycle by a trigger point shock wave and can relieve the symptoms of dysmenorrhoea. Furthermore, no adverse events (AEs) occurred during the follow-up after 6 months.

Therefore, we will use rESWT for treatment in the hope of obtaining imaging evidence of analgesia, especially immediate analgesia. In this trial, we will focus on assessing the therapeutic effect of rESWT treatment and sham rESWT treatment. For an in-depth understanding on the mechanism in terms of central analgesia of pain relief by rESWT, the changes in pain state, emotional state and local brain functional areas will be assessed before and after the therapy.

## Methods

### Objectives

Our objectives are to: 1) evaluate the efficacy of rESWT in the treatment of PDM compared with the placebo group; and 2) explore the central mechanism of rESWT in the treatment of PDM according to the results of resting functional magnetic resonance imaging (fMRI).

### Design

This study will be a randomised, assessor- and statistician-blinded, placebo-controlled trial. A total of 36 subjects with PDM who meet the guidelines of the Society of Obstetricians and Gynaecologists of Canada for the diagnosis of PDM will be recruited and randomly assigned to a shock wave group or a sham shock wave group at a 1:1 ratio. Table 1 lists the recruitment process, intervention methods and evaluation, and Fig. 1 depicts the experimental flow chart. The Standard Protocol Items: Recommendations for Interventional Trials (SPIRIT) 2013 checklist is attached as Additional file 1. This study commenced in January 2019 at the Zhongshan-Xuhui Hospital, Fudan University, Shanghai, China.

**Table 1 Tab1:** Study design schedule

Period	Screening	MRI scan	Treatment	MRI scan	Close-out
Menstrual cycle	0 month	1 month	1 month	1 month	1 month
Inclusion and exclusion criteria	√				
Informed consent	√				
Physical examination	√				
Medical history	√				
Comorbidities	√				
Pelvic MRI	√				
Allocation			√		
SF-MPQ		√		√	
CMSS		√		√	
SAS and SDS		√		√	
Patient compliance					√
Reasons for dropout or withdrawals					√
Adverse events					√
Safety evaluation					√

*CMSS* COX Menstrual Symptom Scale, *MRI* magnetic resonance imaging, *SAS* Zung Self-rating Anxiety Scale, *SDS* Self-rating Depression Scale, *SF-MPQ* Short form of the McGill Pain Questionnaire

**Fig. 1 Fig1:**
[figure not shown]
Flow chart of the trial. fMRI functional magnetic resonance imaging, rESWT radial extracorporeal shock wave therapy

### Experimental ethics

The ethics-related aspects of this research were approved by the Institutional Review Board of the Institute of Clinical Trials. The experiment was reviewed and approved by the Ethical Committee of Zhongshan-Xuhui Hospital in January 2019 (approval no. 2018043). The study was registered in the Chinese Clinical Trial Registry in January 2019 (ChiCTR1900020678). This research conforms to the Helsinki Declaration.

Demographics data (height, weight, occupation, family history of dysmenorrhea, years of menstruating, age of onset of dysmenorrhea, menstrual cycle, number of days of menstruation, duration of dysmenorrhea per month (hours), aggravating/alleviating pain factors), questionnaire results, MRI results and signed consent forms will be gathered. All electronic data will be stored in encrypted computers and paper data will be locked in cabinets.

Any modification of the protocol will be documented at www.chictr.org.cn. The research team will disseminate the results of this study by publishing them in peer-reviewed journals.

### Participants

#### Recruitment

Subjects will be recruited from the Shanghai University of Sport, East China Normal University and the Shanghai University of Medicine and Health Sciences through recruitment posters.

#### Exclusion criteria

The exclusion criteria are as follows:
Mental or neurological disorderHistory of childbirthEarly pregnancy or immediate plans for pregnancy [16]Allergy to the coupling agentHistological changes in the skin or muscle of the treatment siteSevere mental illnessSerious diseases, such as those of the heart, brain, liver, kidney and haematopoietic systemContraindications to MRI (claustrophobia, pacemaker implants or surgical metal plate in the body)

#### Termination criteria

The criteria for termination of subjects with PDM are as follows:
Subjects taking other forms of pain relief, such as extra pain relievers, during the rESWT treatment period of this trialSerious AEs (SAEs)Surgery or hospitalisation for an accident or other diseasesParticipant request

A reminder will be sent the day before the appointment to ensure participant retention and adherence.

### Randomisation, concealment of allocation and blinding

Participants who meet the inclusion criteria will sign the informed consent form voluntarily and will be eligible for randomisation. They will be assigned randomly to the rESWT group or the sham rESWT group. The random sequence will be generated by a statistician using IBM® SPSS® statistics version 22.0 (IBM Institute, Inc., USA) who is not involved in the intervention or outcome evaluation.

The random number and group assignment will be sent immediately to the independent assessor by another research coordinator via an encrypted electronic file. As much as possible, evaluators will be prevented from communicating with the patients to avoid bias. This process will ensure that randomisation concealment will be competent and will be unaffected by the participants or practitioners.

It is not feasible for the therapist and the patient to be double blind because of the particularity of shock wave therapy. Before signing the informed consent form, patients will be told that they will receive shock wave treatment. Participants will not know their treatment allocation. The therapist will not be blinded, but will not assess the effectiveness of the treatment. Outcome assessors, data managers and statisticians will be blinded to treatment allocation. Prior to the start of the trial, all researchers will be trained to ensure the successful implementation of the blinding procedure.

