#### Secondary outcomes

##### Zung SAS

The Self-rating Anxiety Scale (SAS) will be used to measure anxiety-related symptoms in PDM since dysmenorrhoea is often accompanied by emotional change. It is a self-administered questionnaire, with each response using a four-point scale from 0 (none of the time) to 4 (most of the time). A total score above 40 indicates a clinically relevant anxiety disorder [20]. The SAS will be utilised before and after rESWT treatment (Table 1).

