The limitations of this trial should be mentioned. A sham radial extracorporeal shock wave group will function as the control group in this study. Since no research is available on reliable treatment using sham shock waves, the principle of controlling with no energy output in previous clinical studies is applied. However, limitations occur with any type of sham shock wave. First, this is not a double-blind trial because those conducting the treatment cannot blindly assign treatment without knowing the type of treatment. To minimise the risk of bias, participants and evaluators will be carefully identified for their shock-wave types and trained in advance to apply a sham shock wave with the machine vibrating and pushing onto the handle with almost no energy. Second, a shock wave often shows a large nonspecific effect and produces physiological activity, which cannot be ignored during the experiment. Nonetheless, the neural mechanisms between different groups can be compared. Therefore, by using the MRI results, we can recognise rESWT-specific pathways related to pain amelioration, even if their effects are not significantly different. Third, a healthy group should not be used as a control group. Previous literature has shown differences in the brain networks of patients with PDM and healthy participants [27, 28]. Conversely, our study will focus on the functional brain changes that will be confirmed by extracorporeal shock wave rather than the PDM-specific features against healthy controls. Therefore, the comparison of the changes in brain networks between the rESWT and sham rESWT groups will be emphasised. Thus far, the randomised controlled trial has only been exploratory, but the prospects look promising. In the future, we expect to collect extensive samples with higher-quality randomised controlled trials.

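### The allocation procedure sends the group assignment to the independent assessor, although the plan says outcome assessors are blinded; both statements cannot hold

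*Protocol article*

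**What the plan says.** The Design section sets out the blinding: "This study will be a randomised, assessor- and statistician-blinded, placebo-controlled trial". The section on randomisation, concealment of allocation and blinding confirms it: "Outcome assessors, data managers and statisticians will be blinded to treatment allocation".

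The same section describes how the allocation travels once the sequence exists: "The random number and group assignment will be sent immediately to the independent assessor by another research coordinator via an encrypted electronic file". The next sentence offers a safeguard: "As much as possible, evaluators will be prevented from communicating with the patients to avoid bias". The section then presents this process as what secures concealment.

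Two other roles are covered there. On the person giving treatment: "The therapist will not be blinded, but will not assess the effectiveness of the treatment". On the participants: "Participants will not know their treatment allocation".

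In Table 1, allocation is ticked in the treatment column. The SF-MPQ, CMSS, SAS and SDS are ticked in the MRI columns before and after it.

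**The concern.** An assessor who is sent the group assignment is not blinded to it. The article claims assessor blinding as a feature of the design, and the operative sentence on allocation contradicts that claim.

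The claim carries weight in this trial. The therapist is unblinded by necessity, the Discussion concedes that any sham shock wave has limitations, and both primary outcomes (SF-MPQ and CMSS) are subjective scales. If staff followed the sentence literally, the trial could not accurately be reported as assessor-blinded. An assessor who knew the arm could affect how a scale is introduced, prompted or scored.

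**Working it through.** No figure is involved, so there is nothing to recompute. The check compares the statements and their order in time.

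**1. The statements side by side**

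| Question | What the protocol article states | Where |
|---|---|---|
| Who receives the assignment? | The independent assessor, immediately | Randomisation section |
| Are outcome assessors blinded? | Yes | Randomisation section; Design |
| Who needs the assignment to treat? | The unblinded therapist, who has no outcome role; not named as a recipient | Randomisation section |
| When is allocation made? | In the treatment period | Table 1 |
| When are the scales completed? | Once before and once after treatment | Table 1 |

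The first two rows conflict unless something else in the text separates them.

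**2. Does anything separate them?**

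- *Encryption.* It protects the file in transit. It does not hide the content from the addressee.
- *Masking.* The item sent is the random number together with the group assignment. Nothing says that the group is coded.
- *A different assessor.* The recipient is called independent, while the blinding sentence speaks of outcome assessors. The article defines no assessor whose duties exclude outcomes, and the sentence after the transfer turns to evaluators and bias. The natural reading is the outcome assessor.
- *Restricted contact.* The restriction applies only as far as possible. It narrows the opportunity to influence a participant but does not remove knowledge already given.

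None of these reconciles the two statements.

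**3. Timing.** The order in Table 1 is first questionnaires and MRI, then allocation and treatment, then second MRI and questionnaires. With immediate transmission, the assignment reaches the assessor after the baseline scales and before the post-treatment scales. The baseline ratings are therefore not touched; the post-treatment ratings are.

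**4. How far could the knowledge act?**

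- SAS: "It is a self-administered questionnaire".
- SDS: the participants complete the 20 items themselves.
- CMSS: the patients rate the severity and duration of their symptoms.
- SF-MPQ: graded pain descriptors, a visual analogue scale and present pain intensity, all resting on the participant's own rating.
- fMRI: processed by software, then interpreted by two radiologists and further analysed by rehabilitation doctors. None of them is named as a recipient of the file.

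The remaining route is the assessor's handling, prompting or scoring of scales that the participant largely rates. The article does not say how much of this the assessor does, so no size can be attached to the bias.

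**The case against.** The strongest reply is that this is a drafting slip. The intent to blind assessors is stated in two sections, the researchers are to be trained in the blinding procedure, and only one sentence conflicts. Nobody is named as passing the assignment to the therapist, so a wrong word for the recipient is plausible. This may well be right, but it does not dispose of the point: the sentence describes an operating step, staff may follow it, and nothing else in the article corrects it.

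A second reply concerns the consequence, and it stands. A reader might infer that every post-treatment evaluation is unblinded. The article does not support that. The clinical scales rest largely on ratings by participants who are said not to know their arm, the fMRI readers are not named as recipients, and no section says that an assessor interviews participants. The restriction on contact, although incomplete, bears directly on the route by which an assessor might cue a participant.

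A reader might also see a second contradiction in the limitations paragraph of the Discussion: "participants and evaluators will be carefully identified for their shock-wave types and trained in advance to apply a sham shock wave". Read literally, the clause would have participants trained to deliver a sham treatment, so it is garbled. It sits in a sentence about reducing bias and cannot reliably be taken to mean that participants or evaluators are told the arm. It should be clarified, but it is not evidence that allocation is disclosed.

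**Conclusion.** The point holds as an internal contradiction about who receives the assignment, and the procedure is wrong as written. Followed literally, it would give the assessor the arm of each of the 36 planned participants before the post-treatment scales, and the claim of assessor blinding would fail.

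This rests on two readings: that the independent assessor has outcome duties, since no other assessor role is defined, and that the assignment is sent uncoded, since no masking is described. If the full protocol shows either to be wrong, the article needs only a clearer sentence.

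The effect on the results is probably limited, because the scales are largely participant-rated and participants are stated to be blinded. Neither its size nor its direction can be derived from the document.

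**What to change.** Change the transfer sentence so that the assignment goes only to the unblinded treating therapist, or to another named person with no outcome role, and is released after the baseline questionnaires and first MRI, which is where Table 1 already places allocation. State that assessors, data managers and statisticians receive study numbers only.

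The Trial status section reports that recruitment began on 31 January 2019 and that seven patients had been selected at submission. A change of wording cannot repair what has already happened. The sponsor should therefore record who actually received the assignments of participants already allocated, and describe assessor blinding for them in the report accordingly. If the sentence was only a slip, that record will show it.

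The unclear clause in the limitations paragraph should be reworded at the same time.

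The cost is one corrected sentence, a different recipient for the file, a short check of the allocation records and one clarified clause. Sample size, outcomes and analysis are unaffected.
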